**Figure 2 figure2:**
[figure not shown]
Flowchart of the study process from recruitment to confirmatory testing. ART: antiretroviral therapy; RDT: rapid diagnostic test.

### Study Population

This is a general population study of adult males and females who are self-reported HIV negative or have an unknown HIV status in order to assess the capability, from device interaction, of identifying those who are potentially at high risk for contracting HIV. Recruitment will take place in different geographical regions using multiple recruitment methods, increasing the chances of the study population being representative of the general population.

### Study Site

Participants will be recruited from three districts situated in three provinces: (1) Tshwane, Gauteng; (2) Gert Sibande, Mpumalanga; and (3) Ugu, Kwa-Zulu Natal. The participating sites comply with all local government requirements for HIV testing and reporting. All sites will receive necessary approvals prior to enrolling participants.

### Sample Size

A purposive sample of 600 participants across all sites (200 per site) will be recruited for this study. In machine learning, the required sample size for a study has not developed into a clear-cut methodology and requires data to compare model performance to relative data size. Therefore, the initial feasibility study maximized on available funding to determine an initial sample size for method validation and to allow for the ability to use the initial sample to compare the performance of the model to the sample size. As seen in Figueroa et al [12], 80-560 samples were required to reach a root-mean-square error below 0.01. A sample size of 600 based on the observations of Figueroa et al [12] will facilitate comparison between model sample size and model performance in order to inform further investigations and machine learning model development. As the device is intended to be used by both males and females from the general population, this assessment aims to recruit as close to a 50% breakdown per gender as possible.

### Inclusion Criteria

This study is open to individuals 18 years of age or older who meet the inclusion criteria. No potential participant will be excluded because of race, gender, ethnicity, or sexual orientation.

People volunteering to be enrolled in this study must meet the following criteria:

Understands and signs the written informed consent formIs able to complete the required testing on the allocated testing day(s)Agrees to provide an accurate medical history and the required specimens for two fingerprick blood testsIs able to speak and read EnglishIs ≥18 years of ageIs willing to provide the required information for the algorithmsIs HIV negative or has an unknown HIV status

### Exclusion Criteria

Participants meeting any of the following criteria will be excluded from the study:

Are known to be HIV positiveHave received any experimental HIV vaccineAre currently on a PrEP regimen or any HIV treatmentCannot provide legal identification for age verificationHave any condition that, in the opinion of the facilitator, would make them unsuitable or unsafe for enrollment; interfere with the completion of the assessment, consent form, and questionnaire; or bias the outcome, for example, being unable to see/read by forgetting to bring reading glasses, being intoxicated, or having acute illness

### Blinding of Results

This will be a blinded study. Participants will not be aware of their risk assessment scores. There will be no randomization of participants, as all participants will be required to interact with the machine-guided tool. This study will make use of supervised learning in which the data set will be collected and then used to train and test the machine learning model that has been created. The data will be collected in a specific area, and selection will be random. The data, however, will be split into training and validation data using a randomized split algorithm commonly found in statistical and data processing languages such as R and Python.

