**Methods:**

In total, 200 HIV-negative adult individuals across three South African study sites each (two semirural and one urban) will be recruited. Study processes will include (1) completing a series of questions (demographic, sexual behavior and history, personal, lifestyle, and symptoms) on an application system, unaided (assistance will only be provided upon user request); (2) two HIV tests (one per study visit) being performed by a nurse/counselor according to South African national guidelines (to evaluate the prediction accuracy of the tool); and (3) communicating test results and completing a user experience survey questionnaire. The output metrics for this study will be computed by using the participants’ risk assessment scores as “predictions” and the test results as the “ground truth.” Analyses will be completed after visit 1 and then again after visit 2. All risk assessment scores will be used to calculate the reliability of the machine-guided tool.

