### Design

In this longitudinal, supervised learning study, the data collected will be split into a training set and a validation set and the data used to validate the model will not be used in the training of the model, which will eliminate the need for a control group. This study will build on the feasibility study described before. The major variable shift is from a clinic-based setting to an in-field setting, which includes rural and semirural sites.

During the evaluation, the untrained user will be assessed thoroughly for process success or difficulty by a silent, non-interacting nurse/counselor. Overall, the process will include (1) completing a series of behavioral questions on an application system without the assistance of trained staff (assistance will only be provided on user request); (2) HIV testing being performed by the trained nurse/counselor (for comparator data to the risk assessment scores); and (3) communicating test results and completing a survey questionnaire developed to collect data on user experience.

All participants will have two rapid HIV tests performed. In the event of a positive HIV diagnosis, the participant will be referred for clinical treatment and care. If a participant tests negative, they will be found eligible for visit 2, which will occur 3 months after visit 1. At visit 2, the participant will follow the same process as that completed at visit 1 (Figure 2).

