#### Skewed Data

The participants enrolled in this study who are either HIV negative or of unknown HIV status will cause a lower HIV prevalence in the sample data set. However, this will be done so as to remove the possibility of participants who are HIV positive creating a bias in the supervised learning, as these people may have altered behavior due to being HIV positive, which may result in risk reduction behavior, reducing the sensitivity and accuracy of the model. The skewed data set will be accounted for in the second phase of the study, where participants will perform two visits, including a follow-up HIV test, which will allow for the analysis of a comparison to the predictive ability of the machine learning model created in phase 1.

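### The training/validation split separates data rather than people, so a returning participant's two records can fall on both sides

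*Protocol article*

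**What the plan says.** **Repeat records.** Under Design, "If a participant tests negative, they will be found eligible for visit 2, which will occur 3 months after visit 1". The same section adds: "At visit 2, the participant will follow the same process as that completed at visit 1". Subject Tool Evaluation confirms that only visit-1 negatives come back. Each returner therefore supplies two questionnaire-and-test records.

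**The split.** Blinding of Results states: "The data, however, will be split into training and validation data using a randomized split algorithm commonly found in statistical and data processing languages". Neither the unit (person or record) nor the proportion is given, nor which visits enter the split.

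**The safeguard.** Design promises that "the data used to validate the model will not be used in the training of the model", and gives this as the reason why no control group is needed.

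**Use of the two visits.** The abstract's Methods say "Analyses will be completed after visit 1 and then again after visit 2" and "All risk assessment scores will be used to calculate the reliability of the machine-guided tool". Skewed Data describes the follow-up HIV test as allowing "a comparison to the predictive ability of the machine learning model created in phase 1". Sensitivity Analysis takes sensitivity, specificity and accuracy from the validation part of the split.

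**The concern.** A validation set measures performance in new people only if it contains no one the model has already learned from. Two records from one person, 3 months apart, are likely to be similar. Gender, race and date of birth do not change, and several questionnaire items look back 6 months or a year, so their windows overlap. The label is also nearly always the same, because only negatives return.

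A standard random split works on rows by default. Applied to data from both visits, it satisfies the wording of the promise in Design while letting the same person sit in training and validation. The same exposure arises without pooling if a model trained on this study's visit-1 data is then evaluated at visit 2 on all returners.

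The effect runs one way. No visit-1 positive has a second record, so recognising a person mostly means recognising a negative. That flatters specificity, overall accuracy and concordance. In the visit-2 evaluation, a person who has seroconverted may be pulled towards a low score by their own earlier negative record, in the cases the tool most needs to flag.

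**Working it through.** **Inputs from the article.** N = 600: "A purposive sample of 600 participants across all sites (200 per site) will be recruited for this study". Check: 3 × 200 = 600, which reproduces. Visit 2 is for visit-1 negatives only.

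**Assumptions (not in the article).** Prevalence at visit 1, p = 3–10%; retention, r = 70–100%; training share, t = 70–80%.

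**Step 1. Both visits pooled and split by row.**

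- Records = N + N(1 − p)r
- Share of records belonging to a pair, f = 2N(1 − p)r / records
- Share of validation records with the same person in training = f × t

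| p | r | t | Second records | All records | f | f × t |
|---|---|---|---|---|---|---|
| 10% | 70% | 70% | 378 | 978 | 0.773 | 0.54 |
| 5% | 85% | 70% | 484.5 | 1,084.5 | 0.893 | 0.63 |
| 3% | 100% | 80% | 582 | 1,182 | 0.985 | 0.79 |

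With a participant-level split the share is 0%.

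**Step 2. Visit-1 model checked at visit 2 on all returners.** If a share t of people trained the model and return is unrelated to the split, then 70–80% of visit-2 participants were trained on, every one labelled negative.

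**Step 3. Effect on the measures.** A simulation compared the two splits using k-nearest neighbour, an algorithm the article lists. Assumptions: 600 people, 30 yes/no items, 90% of answers carried over to visit 2, full retention, 1% seroconversion, 70/30 split, 200 runs per setting. Settings crossed prevalence 5% or 10%, no signal or modest signal, and k = 1 or 5. Two no-signal examples with k = 1:

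| Prevalence | Measure | Row split | Participant split |
|---|---|---|---|
| 5% | Accuracy | 0.956 | 0.934 |
| 5% | Specificity | 0.986 | 0.962 |
| 5% | Sensitivity | 0.031 | 0.037 |
| 10% | Accuracy | 0.924 | 0.880 |
| 10% | Specificity | 0.976 | 0.930 |
| 10% | Sensitivity | 0.059 | 0.072 |

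Across all eight settings the row split raised accuracy by 0.7–4.4 points and specificity by 0.8–4.6 points. Sensitivity was unchanged or lower, by 0–3 points.

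**Step 4. Pull on visit-2 scores.** A separate simulation trained a random forest on the visit-1 records of 70% of people, using invented standard-normal features (6 fixed, 14 varying between visits). At a cut-off flagging 20% of unseen visit-2 participants, it flagged 16%, 12% and 6% of those already trained on, at within-person correlation 0.5, 0.8 and 0.95.

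**Step 5. Standard errors, if any measure pooled visits.** Ignoring the pairing understates the standard error by √(1 + fρ) over all scores, that is 1.18–1.41 for ρ = 0.5–1.0. Inside a row-split validation set the factor is √(1 + f(1 − t)ρ), only 1.04–1.14, because most partner records sit in training.

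**The case against.** The strongest reply is that the article is silent rather than wrong, and that a condensed article may leave the split unit to the full protocol or analysis plan. Several parts of this reply stand.

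- **Independence of records.** A reader might infer that the plan treats records as independent. No sentence says so. Error and Failure Rates defines failure by a person's result at both visits, and Data Analysis looks for people whose test changes between visits, so some measures are already defined within person.
- **Intervals.** A reader might conclude that the error bars are too narrow. The article states no interval method and no significance level; Post Hoc Analysis names only confidence curves. The reliability for which all scores are used is undefined. Any effect on intervals is therefore conditional, and it is small inside a row-split validation set.
- **Every reading.** A reader might say the plan fails however its phases are understood. It does not. If the algorithm comparison uses visit 1 alone, each person has one record and a row split is already a participant split. Skewed Data calls the second phase the one with two visits, so phase 1 may be the earlier feasibility study; a model built only on those people would have no overlap.
- **Similarity.** The partner question covers only 3 months and the last-HIV-test answer will often change after visit 1. No within-person correlation is given.

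What does not stand is that the separation promise already covers the matter. The article itself fixes the split method and rests the absence of a control group on it, and that promise concerns data. Design and Blinding of Results also describe splitting this study's data, so the feasibility-only reading is not secure.

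**Conclusion.** The point holds as a gap in the stated safeguard: the split and the promise of separation do not make the participant the unit in a design that measures returners twice. The consequence is conditional. It arises if both visits enter a row-level split, or if a model trained on this study's visit-1 data is evaluated on all returners. The 54–79% overlap rests on the assumed prevalence, retention and training share. The gain of about 1–5 points in accuracy and specificity rests on a simulation with strong carry-over of answers, and less similarity would give less. Concordance would be inflated by the same mechanism. Sensitivity is not inflated, which matters because Machine Learning Algorithm puts weight on avoiding false negatives. The downward pull on a seroconverter's visit-2 score is a real risk, but its size cannot be known from the article. This is a cheap improvement worth making, not evidence that the planned results would be invalid.

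**What to change.** 1. In Design and Blinding of Results, state that the split, and any cross-validation, is made once by participant ID, with all of a person's records on one side. State which visits train and which validate.
2. For the visit-2 evaluation in Data Analysis and Skewed Data, score each person with a model that did not train on that person. Either evaluate held-out participants only, or use participant-level cross-fitting so that all returners are kept.
3. Report performance separately by visit. If any measure pools visits, cluster its interval by participant, for example by bootstrapping participants.

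**Cost.** A change of wording and a grouped split in R or Python. No extra participants, visits or data are needed. Reported performance will be slightly lower, and cross-fitting adds a little computing.

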A risk assessment tool is a set of simple and easy*-*to*-*understand questions *that* are answered by the participant(s)*,* and based on the responses, a risk probability is calculated. The questions are related to demographics, sexual behavior, sexual history, personal behavior, lifestyle*,* and medical history. The questions are scientifically designed based on the HIV correlation data from published research and clinical trials. The tool makes use of scientific algorithms to determine the risk probability and *provides* the outcome as low risk*,* medium risk*,* or high risk. Diagnostic assistive assessment is performed on a mobile device by the patients themselves*,* thus eliminating external influences and hence providing more accurate information.

In 2019-2020, a feasibility study was conducted with over 1000 participants at the Wits Reproductive Health and HIV Institute’s (WRHI) HIV self-testing assessment and research (HSTAR) Africa site in Johannesburg, South Africa. This study sought to understand the correlation between HIV status and factors such as demographics, sexual behavior and history, personal behavior and lifestyle, and symptoms, individually.

Analysis of the data collected from this feasibility study showed correlations between HIV status and all the variables. The main inference made was that patients can be grouped based on multiple factors as follows:

Primary features (demographics)Secondary features (lifestyle)Tertiary features (sexual behavior)Auxiliary features (symptoms)

Examples of the detailed analysis are shown in Figure 1.

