#### Sensitivity Analysis

The performance of the model will be analyzed using the validation data set from the data split using a confusion matrix (Figure 5) that will allow for the calculation of sensitivity, specificity, and accuracy.

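### Measuring sensitivity on the validation part of a random split of 600 low-prevalence participants leaves it resting on few HIV positives (about 4 to 18 if prevalence is 3-10% and the validation share 20-30%); stratified cross-validation would use them all

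*Protocol article*

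**What the plan says.** Three sections of the protocol article describe how performance is measured.

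- Design: "the data collected will be split into a training set and a validation set". The section adds that the two sets are kept apart.
- Blinding of Results: "The data, however, will be split into training and validation data using a randomized split algorithm". It names R and Python as typical software and gives no further detail.
- Sensitivity Analysis: "The performance of the model will be analyzed using the validation data set from the data split using a confusion matrix". Sensitivity, specificity and accuracy are calculated from that matrix.

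The size and make-up of the data come from two other sections.

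- Sample Size: "A purposive sample of 600 participants across all sites (200 per site) will be recruited for this study". The justification is a cited finding that "80-560 samples were required to reach a root-mean-square error below 0.01". No target number of HIV-positive people is set.
- Skewed Data: enrolling only people who are HIV negative or of unknown status "will cause a lower HIV prevalence in the sample data set". The section relies on a second phase with a follow-up test to deal with this.

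Machine Learning Algorithm compares six algorithms by confusion matrix and gives weight to avoiding missed high-risk people, which puts sensitivity in front. The Abstract, by contrast, says that all risk scores enter the reliability calculation. That does not fit easily with a validation-only analysis.

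**The concern.** Sensitivity is estimated only from people who test positive. The article expects few of them among 600, and a hold-out then uses only the fraction that falls in the validation set. The positives in the training set contribute nothing to the estimate.

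Two things follow. The interval around sensitivity may be too wide to say whether the tool finds most infected people. And the point estimate depends partly on which few positives the random split happens to place in validation. Both concern the measure that matters most to the article's stated wish to avoid false negatives. This is separate from any optimism caused by choosing the best algorithm on the same data that are used to report it.

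**Working it through.** **Inputs from the article.** Total sample 3 x 200 = 600, which agrees with the stated total. Training and validation sets are disjoint. Performance comes from the validation set. The article gives no prevalence, split share or precision target, so it has no figure of its own for the precision of sensitivity to reproduce.

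**Assumptions.** HIV prevalence at testing 3-10%; validation share 20-30% (120 to 180 people); observed sensitivity near 80%, for illustration.

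**Step 1: expected positives in validation** = 600 x share x prevalence.

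| Prevalence | All positives | 20% validation | 30% validation |
|---|---|---|---|
| 3% | 18 | 3.6 | 5.4 |
| 5% | 30 | 6 | 9 |
| 10% | 60 | 12 | 18 |

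This gives about 4 to 18. Wider assumptions give about 1 (1% prevalence, 20% share: 1.2) to 36 (20% prevalence, 30% share).

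**Step 2: precision of sensitivity on the validation set** (exact Clopper-Pearson 95% intervals).

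- 3 of 4: 19-99%
- 7 of 9: 40-97%
- 14 of 18: 52-94%

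**Step 3: variation from the split alone.** Under a random split without stratification, the number of positives in validation is hypergeometric.

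- 30 positives, 30% share: mean 9, 95% range 4 to 14.
- 18 positives, 20% share: mean 3.6, 95% range 1 to 7, with a 1.7% chance of none at all.

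Stratifying would fix the count but not which positives are drawn. Suppose a fixed classifier detects 24 of 30 positives (80%) and 9 of the 30 fall in validation. The number detected among those 9 is hypergeometric (30, 24, 9), with mean 9 x 24/30 = 7.2 and 95% range 5 to 9. Observed sensitivity then runs from 5/9 = 56% to 9/9 = 100%, with nothing changed but the draw.

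**Step 4: every participant gets an out-of-fold prediction.** All positives count, which is 1/0.30 = 3.3 to 1/0.20 = 5 times as many. Approximate 95% intervals:

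- 3% prevalence, 14 of 18: 52-94%
- 5% prevalence, 24 of 30: 61-92%
- 10% prevalence, 48 of 60: 68-89%

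Like for like, at 5% prevalence and a 30% share the interval narrows from 40-97% to 61-92%; at 10% and 30% it narrows from 52-94% to 68-89%; at 3% and 20% it narrows from 19-99% to 52-94%.

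**Step 5: does visit 2 repair this?** It adds only people who convert within 3 months. With about 570 people followed (600 x 0.95) and an assumed annual incidence of 0.5-4%, new positives = 570 x incidence x 0.25, or 0.7 to 5.7. These cannot repair the precision of the split on which the model is first assessed.

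**The case against.** The strongest reply is that this is a condensed article. A randomized split algorithm may be stratified or repeated, and the split share and resampling scheme are details that a full protocol or analysis plan usually carries. Hold-out validation is also an accepted method, and Sample Size presents the study as a step towards further model development. Part of this stands: a reader might infer that the split is known to be unbalanced on HIV status, but the article only leaves balance unstated. What remains is that the article does state a method, a division into a training set and a validation set with performance read from the latter, and stratification alone would not bring the training positives into the estimate.

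A second reply is that performance is not measured on the validation part alone. The Abstract uses all risk scores, Data Analysis makes concordance of the score with the test the endpoint and analyses all recorded scores, and Error and Failure Rates takes all completed cases as its denominator. This stands as an inconsistency to reconcile. It does not remove the text of Sensitivity Analysis, which places sensitivity, specificity and accuracy on the validation set.

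Four further readings are tempting and not supported.

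- That 4 to 18 is the plan's own number. It depends on an assumed prevalence and split share.
- That two splits could reverse the study's conclusion. The article sets no success threshold, so only variation of the estimate can be shown.
- That the earlier data are left out of the model fit. The Introduction reports that "a feasibility study was conducted with over 1000 participants", and Design says the present study builds on that work; the role of those data in fitting is unclear, not excluded.
- That the questionnaire has too many inputs for the training positives. Interaction Between Variables plans bivariate analysis and feature engineering, so the number of fitted inputs is unknown.

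**Conclusion.** The point holds in a conditional form. The stated method sets aside most positives when sensitivity is measured, in a sample where the article itself expects few. With 3-10% prevalence and a 20-30% validation share, sensitivity rests on about 4 to 18 people, and the exact 95% intervals are about 41 to 80 percentage points wide (94 - 52 = 42 from rounded limits at best, 99 - 19 = 80 at worst). With 9 validation positives the draw alone moves an 80% sensitivity between 56% and 100%.

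A reader might infer that using all 600 people solves the problem. It does not: at 3% prevalence all 18 positives give about 52-94%, the same interval as the best hold-out case in this range. The limit there is the number of positives recruited. Cross-validation removes dependence on a single split and improves precision at any given prevalence. The change is worth making because it is cheap, but the concern does not invalidate the study.

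**What to change.** In Design, Blinding of Results and Sensitivity Analysis, replace the hold-out by repeated k-fold cross-validation, stratified on HIV status. Keep every modelling step inside the folds, including feature engineering and the choice among the six algorithms. Compute sensitivity and specificity from the out-of-fold predictions of all participants, and report each with an interval and the number of positives behind it.

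Reconcile Sensitivity Analysis with the Abstract by stating which participants' scores enter which measure.

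State what role the feasibility data have. Where their items match the present questionnaire, fitting on those data and keeping all 600 field participants for external validation is an option, not a requirement.

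The cost is computing time and rewording, with no new participants or visits; the feasibility option also needs a check that the items match. The downside is that out-of-fold predictions are not independent, so binomial intervals on them are approximate and should be labelled so.
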